##### Psychology, cost-effectiveness and mental health substudies

Data will be collected from 30 maternity units preimplementation (sequences 2–6) and 30 postimplementation (sequences 1–5). The sample size calculation is based on recruitment of mothers experiencing PPH and requires 40 to be recruited per maternity unit over a 6-month period preimplementation and the same number again postimplementation (allowing for 75% attrition, as observed during the early stages of this study) at 6-month follow-up. This will provide ≥80% power for a medium effect size (Cohen’s delta of 0.5) based on a two-sided alpha of 5% and assuming an approximate normal distribution of outcome data. Maternity units will recruit a comparator group of mothers who have experienced a PPH and their birthing partners.

The same women and partners will be recruited for the psychology and cost-effectiveness substudies. The cost-effectiveness study will also recruit up to 40+40 women and economic partners (EP) who did not experience a PPH from before and after the intervention.

At least 10 women and birth partners who report high levels of PTSD symptoms and at least 10 birth partners reporting low levels of PTSD symptoms recruited from the preimplementation psychology substudy will be interviewed in the mental health substudy.

##### Process evaluation

The process evaluation includes 3 days of ethnographic observations during each phase of the OBS UK study. Retrospective case studies involving interviews with 5–6 staff and 2–3 women who experienced a PPH >1 L will be conducted in four Welsh OBS Cymru maternity units.^38^ Prospective case studies in six sites (one per sequence) will include interviews with 12–15 maternity team members sampled across the three study phases and approximately four women who have had a PPH >1 L and their birth partners from the usual care and OBS UK care phases.

##### E-Fib substudy

Based on data from our recent publication and theoretical modelling,^26
29^ we anticipate that the proportion of women with fibrinogen level <2 g/L during obstetric haemorrhage who achieve a fibrinogen level of >2 g/L after the first cycle of coagulation product transfusion will increase from 30% with usual treatment to 70% with OBS UK treatment. To detect an effect of this magnitude with 90% power with a two-sided 5% type I error rate, 62 women are required (based on a χ^2^ test). To account for up to 22.5% missing, the sample size is inflated to 80 women (40 receiving usual treatment and 40 OBS UK treatment).

### Randomisation

Maternity units were randomised all at once by the trial statistician to one of six sequences before the start of the study using R. A covariate-constrained randomisation procedure was used to ensure that half the maternity units in each sequence were allocated to ROTEM and half to TEG. This approach was used to prevent severe imbalances with respect to size of maternity unit (births per year) both between maternity units using different types of devices within the same sequence and between sequences. The final allocation was selected at random after discarding the worst 10% of possible allocations with the highest imbalance.

### Main analysis

Clinical and sociodemographic characteristics of women in participating maternity units as well as unit characteristics will be summarised descriptively and graphically.

The primary analysis will be intention-to-treat, meaning that all participants will be analysed as receiving usual care or OBS UK care (including data from women in months 5–9 of the implementation period) according to the randomisation status of their obstetric unit, regardless of adherence to the intervention. The primary estimand will use a treatment policy strategy for intercurrent events. It will use a logistic mixed-effects regression model with cluster (maternity unit) and cluster-time interaction fitted as random effects, fixed effects for time period (to capture secular trends) and exposure status as well as fixed effects for the stratification variables (unit size and point-of-care device) to estimate the OR of receiving RBC transfusion for PPH between OBS UK care and usual care, presented as a point estimate with a two-sided 95% CI and p value. If the estimate favours OBS UK care and the 95% CI excludes one, effectiveness of the intervention will be concluded. Similar analyses will be performed for the secondary clinical and psychological outcomes with linear instead of logistic models used for continuous outcomes for which at least approximate normality can be assumed.

Sensitivity analyses may consider alternative correlation structures, secular trends that differ between (randomised groups of) units, and intervention effect heterogeneity across time and/or (randomised groups of) units.^39
40^ In a further sensitivity analysis, a marginal mean model will be fitted using generalised estimating equations with robust SEs instead of mixed-effects regression, allowing a more population-focused interpretation.^41^

Subgroup analyses will explore the impact of ethnicity and/or socioeconomic factors and other aspects of demographic diversity on the intervention effect, by adding interaction terms with intervention to the analysis model.

If some units implement individual elements of the OBS care bundle prior to entering the 9-month implementation period, or if individual units fail to implement the intervention during the 9-month period, this will be modelled in a separate sensitivity analysis. No unit will have adopted the point-of-care tests of coagulation or used QI methods for implementation of the entire OBS UK care bundle prior to the 9-month implementation period. The variation in prior adoption and/or partial implementation of individual elements will also be measured and considered in the process evaluation. The process evaluation will include exploring the role of sociodemographic and ethnic differences in staff and patient populations and build on the principles of equality, diversity and inclusion (EDI) in the analysis. A combination of Normalisation Process Theory and the Consolidated Framework for Implementation Research will be used to analyse data.^42
43^ Currently, neither framework attends explicitly to intersectionality nor EDI concerns, but these theories will be developed in this regard.

A statistical analysis plan will be agreed and signed off prior to database lock. Reporting of results will follow the Consolidated Standards of Reporting Trials (CONSORT) statement and its extension to stepped wedge cluster randomised designs.^44^

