### Data analysis and statistics

#### Sample size

##### Primary outcome

The anticipated reduction in RBC transfusion from 27.5 to 18.0 per 1000 maternities is based on the effect size seen in the OBS Cymru pilot study and recently published UK PPH transfusion rates.^9
23^ The average unit size was anticipated to be about 3000 maternities per year.^35^ A stepped wedge cluster randomised trial (using maternity units as clusters) recruiting over 30 months, with 6 sequences and an estimated average of 750 maternities per 3-month period per unit, requires 5 units to be randomised to each sequence. The total of 30 units gives 93% power to detect the above effect size, based on a two-sided type I error rate of 5% and assuming a ‘discrete-time decay’ correlation structure with intra-class correlation of 0.002 (based on previous audit data and similar studies,^36^ and cluster auto-correlation of 0.80 while assuming no data from the 9-month implementation phase will be included in the analysis). With data from implementation months 5–9 included in the analysis (reflecting an assumption that transition to OBS UK care will be underway after 4 months) we will have 90% power to detect a reduction in the primary outcome from 27.5 to 22.0 RBC transfusions per 1000 maternities. The computations were performed using the Shiny CRT Calculator.^37^ One additional unit per sequence will be randomised (total of 36 units) to account for potential drop-out. Based on a more recent estimate of average maternity unit size of 3500 maternities per year, this corresponds to approximately 270 000 maternities to be included in the analysis. The primary outcome is collected monthly from each site using aggregate data and we do not anticipate missingness within the dataset.

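### The sample size names a decaying within-unit correlation, the primary model assumes none, and the stated powers fit the model rather than the named structure

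*Protocol article*

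**What the plan says.** In the protocol article, the sample size section for the primary outcome describes the calculation as "assuming a ‘discrete-time decay’ correlation structure with intra-class correlation of 0.002" and "cluster auto-correlation of 0.80 while assuming no data from the 9-month implementation phase will be included in the analysis". On that basis 30 units, 6 sequences and 750 maternities per unit per 3-month period are said to give 93% power for "The anticipated reduction in RBC transfusion from 27.5 to 18.0 per 1000 maternities". With implementation months 5–9 added, the same section claims "90% power to detect a reduction in the primary outcome from 27.5 to 22.0 RBC transfusions per 1000 maternities". It then raises the number of units to 36 and the average unit size to 3500 per year.

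The Main analysis section fixes the primary model as a "logistic mixed-effects regression model with cluster (maternity unit) and cluster-time interaction fitted as random effects", with fixed effects for period, exposure, unit size and device. Effectiveness is declared if the estimate from this model favours the intervention and its 95% CI excludes one. On the correlation, the section adds "Sensitivity analyses may consider alternative correlation structures". It also commits to a GEE model with robust standard errors as a further sensitivity analysis. The article gives no reason for the difference between the planning structure and the fitted one.

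**The concern.** Independent random intercepts for unit and unit-by-period imply one constant correlation between a unit's effects in any two different periods. Under discrete-time decay at 0.80 per quarter, that correlation is 0.80 for adjacent quarters but 0.80^9 = 0.13 for quarters 27 months apart. A stepped wedge estimate leans on comparisons within units over time. A model that overstates how alike distant periods are will therefore overstate the precision of those comparisons.

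Two things are at stake: whether the 95% CI that decides the trial has its nominal coverage, and whether the stated powers belong to the design and structure described.

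**Working it through.** **Inputs** (protocol article). 30 months, taken as ten 3-month periods. Sequence s has s usual-care quarters, 3 implementation quarters, then 7 − s intervention quarters. ICC ρ = 0.002 and auto-correlation r = 0.80. There are 30 units at 750 per quarter, or 36 units at 3500/4 = 875. Two-sided alpha is 5%.

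**Formula.** For unit-period means with fixed period effects,

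Var(θ̂) = [(Σ X′V⁻¹X)⁻¹]θθ, with V = σ²[ρR + diag((1 − ρ)/m)],

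where σ² is the average of p(1 − p) over the two rates. R has off-diagonal entries r^|t−u| under decay, and r throughout under nested exchangeable. Power = Φ(δ/SE − 1.96).

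**Step 1: the plan's powers.** The first row excludes implementation data. The second includes months 5–9, coded as two thirds of the second implementation quarter plus all of the third. SEs are per 1000; 30 units, 750 per quarter.

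| Contrast | Stated | Decay | Nested exchangeable |
|---|---|---|---|
| 27.5 to 18.0 | 93% | SE 3.32; Φ(9.5/3.32 − 1.96) = 82% | SE 2.76; Φ(9.5/2.76 − 1.96) = 93% |
| 27.5 to 22.0 | 90% | SE 2.21; Φ(5.5/2.21 − 1.96) = 70% | SE 1.78; Φ(5.5/1.78 − 1.96) = 87% |

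Counting two full implementation quarters moves the second row to 73% under decay and 89.7% under nested exchangeable. A t reference with 28 degrees of freedom lowers the first decay figure to 79%. The 93% is therefore reproduced under nested exchangeable and not under decay, and the 90% is also much closer to nested exchangeable.

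For 36 units at 875 per quarter, decay gives SE 2.93 and Φ(9.5/2.93 − 1.96) = 90% for the first contrast, and SE 1.95 and Φ(5.5/1.95 − 1.96) = 81% for the second.

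**Step 2: type I error if decay is true and the planned model is fitted.** The variance components to which REML would converge were found by minimising the expected REML criterion under decay. The model-based SE was then compared with the true (sandwich) SE. With 36 units, 875 per quarter, months 5–9 included and p = 0.0275:

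- model SE 1.86, true SE 2.16, ratio 1.161;
- type I error = 2Φ(−1.96/1.161) = 9.1%.

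Other settings, planned model fitted throughout:

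| Setting | Type I error |
|---|---|
| 30 units, 750 per quarter | 8.8% |
| Auto-correlation 0.90 | 7.7% |
| Auto-correlation 0.95 | 6.6% |
| Implementation data excluded (30 units, 750) | about 7% |
| Simulated binomial cells, REML-type fit, Wald | 8.9–9.9% |
| Same simulations, t reference | 7.4–8.8% |
| Monthly periods, 0.80 per quarter | 14–16% |
| Simulated maximum-likelihood logistic model (36 units, 875) | 11.9% |
| Truth is nested exchangeable (REML-type fit) | 5.2% |

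The simulations put the ICC on the logit scale as 0.002/[p(1 − p)], which is an assumption. Fitting the matching AR(1) model by maximum likelihood in the same simulation still gave 7.4%. So about 4 points of the 11.9% come from the wrong structure, and part of the rest is small-sample error. The lowest value found at 0.80 was 6.2%, which needs both a t reference and exclusion of the implementation data that the primary analysis includes.

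**The case against.** A reader might infer that the primary test simply has a 9% false-positive rate. The document does not support that unqualified reading. Nested exchangeable is a legitimate structure, and the planned model keeps close to its nominal level when that structure holds. The 93% is what the stated inputs give under nested exchangeable, so the words "discrete-time decay" may themselves be the mistake. Planning and analysis would then agree.

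The 9% also rests on quarterly analysis periods and a Wald interval. The article fixes neither of these, nor any small-sample correction, and may properly leave them to the SAP. In addition, the GEE analysis with robust standard errors is a firm commitment, and it addresses a misspecified working correlation, small-sample performance aside.

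All of this stands, and it limits the claim without removing it. If the label is wrong, the sample size section misdescribes its own calculation. If it is right, both powers and the deciding interval are affected. The GEE and the optional alternative structures are sensitivity analyses, and neither governs the conclusion of effectiveness.

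**Conclusion.** The named correlation structure, the stated powers and the primary model do not agree, and this holds on either reading.

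- **If decay is the real assumption:** the powers for 30 units at 750 per quarter are about 82% and 70%, not 93% and 90%. The planned model's CI is too narrow. Type I error is about 9% for quarterly periods, months 5–9 included and a Wald test, and roughly 7–16% over other readings at an auto-correlation of 0.80.
- **If nested exchangeable was used for planning:** the label is wrong, the 93% stands, the 90% is 87–90% depending on how months 5–9 are counted, and type I error is close to 5%.

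The article does not show which of these holds. The size rests on ten equal quarters, equal unit sizes in the analytic figures, and random effects specified as independent, as is usual for the wording used.

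**What to change.** Reconcile the sample size and Main analysis sections before the SAP is signed, which the article places ahead of database lock.

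- **If decay is meant:** make discrete-time decay (unit-level AR(1) effects over period) the primary random-effects structure and keep nested exchangeable as the sensitivity analysis. Specify a small-sample correction as part of the primary analysis, because the decay model alone did not restore 5% under maximum likelihood. Restate the powers: about 82% and 70% for 30 units at 750 per quarter, or about 90% and 81% for 36 units at 875.
- **If nested exchangeable was used:** correct the label, recheck the 90% and say how months 5–9 were counted. Replace the optional wording on correlation structures with a commitment to a decay-structure sensitivity analysis.

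The cost is SAP wording and one model option on 36 × 10 unit-period cells. The price is a slightly wider CI and a less favourable stated power. If nested exchangeable were true, fitting decay raised the SD of the log odds ratio only from 0.0614 to 0.0625 in simulation, with type I error 5.8%. That check used REML on empirical logits with 500 trials, so the 5.8% carries a standard error of about 1 point.

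### The GEE sensitivity analysis names robust SEs without a small-sample correction; run in the usual uncorrected form with 36 units, its nominal 5% error rate would be roughly 6.5 to 9%

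*Protocol article*

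**What the plan says.** The primary analysis (Main analysis) is a logistic mixed-effects model with fixed effects for period, exposure, unit size and point-of-care device. The decision rule is tied to that model: "If the estimate favours OBS UK care and the 95% CI excludes one, effectiveness of the intervention will be concluded".

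A population-averaged analysis follows as a further sensitivity analysis: "a marginal mean model will be fitted using generalised estimating equations with robust SEs", in place of the mixed model. Its stated purpose is an interpretation closer to the population level. The other sensitivity analyses in that paragraph are optional; this one is a commitment. No small-sample correction, reference distribution or working correlation is named.

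Under Sample size (Primary outcome), 30 units are required and 36 are randomised, the extra six being there "to account for potential drop-out". The design is a stepped wedge over 30 months "with 6 sequences and an estimated average of 750 maternities per 3-month period per unit". The type I error rate is 5%, two-sided. The same section assumes an ICC of 0.002 and a cluster auto-correlation of 0.80 with discrete-time decay.

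**The concern.** The sandwich variance takes its information from the number of independent clusters, not the number of women. About 270 000 maternities do not help if they sit in 36 units. With few clusters and many fixed effects, residuals are pulled towards zero by the fit, so the uncorrected sandwich is biased downward. Normal-based limits also ignore the sampling variability of the variance estimate. Both errors make the interval too narrow.

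This is the one analysis offered for a population-level reading of the effect. If its intervals are too narrow, it will agree with a borderline positive primary result somewhat more often than it should.

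**Working it through.** **Inputs from the article.** 36 units in 6 sequences; 30 months in 3-month periods, so 30 / 3 = 10 periods; control rate 27.5 per 1000; ICC 0.002; cluster auto-correlation 0.80; implementation months 5 to 9 counted as OBS UK care; updated unit size 3500 a year, so 3500 / 4 = 875 per period.

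**Assumed, because the article does not give them.** The coefficient of variation (CV) of unit size (0 to 0.5) and the GEE working correlation (independence or exchangeable in the table below).

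**Check of the layout.** Analysed months per unit: 30 − 9 + 5 = 26. Maternities: 36 × 26 × 3500 / 12 = 273 000, which matches the article's figure of about 270 000. The article gives no error rate for the GEE analysis; the benchmark is the nominal 5%.

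**Parameters against clusters.** 10 for the periods (including the intercept) + exposure + device + unit size = 13 fixed effects, against 36 clusters.

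**Simulation under no effect.** Binomial counts per unit and period, discrete-time decay, 3000 to 5000 trials per row, Monte Carlo SE 0.4 to 0.5 percentage points. Rejection rates at nominal two-sided 5%; the t limits use units minus 2 degrees of freedom (34 or 28).

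| Units | Working correlation | Size CV | ICC | Uncorrected, z | Mean SE / true SD | Kauermann-Carroll type, t | Mancl-DeRouen, t |
|---|---|---|---|---|---|---|---|
| 36 | independence | 0 | 0.002 | 7.6% | 0.94 | 5.5% | 4.6% |
| 36 | independence | 0.3 | 0.002 | 8.4% | 0.92 | 5.9% | 4.3% |
| 36 | independence | 0.4 | 0.002 | 8.8% | 0.90 | 6.5% | 4.8% |
| 36 | independence | 0.5 | 0.002 | 9.2% | 0.89 | 6.5% | 5.2% |
| 36 | independence | 0.4 | 0.005 | 9.1% | 0.89 | 6.4% | 5.0% |
| 36 | independence | 0.4 | 0.0005 | 8.5% | 0.91 | 5.6% | 4.5% |
| 36 | exchangeable | 0.3 | 0.002 | 7.8% | 0.93 | 6.1% | 4.9% |
| 36 | exchangeable | 0.4 | 0.002 | 7.9% | 0.92 | 6.1% | 5.0% |
| 30 | independence | 0.4 | 0.002 | 10.6% | 0.87 | 7.0% | 5.2% |

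**Plausibility by hand.** If the SE is too small by a factor r, the rejection rate from bias alone is 2 × [1 − Φ(1.96 r)]. For r = 0.94 this is about 6.5%, and for r = 0.89 about 8%. The simulated 7.6% and 9.2% lie about one point higher, as expected because the SE itself varies. A t reference with 34 degrees of freedom on the uncorrected SE still gives 6.7 to 8.1% with 36 units, so changing the reference distribution alone is not enough.

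**Agreement with other runs.** Two further sets of null simulations with 36 units gave:

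- 7.2 to 7.7% under discrete-time decay and 7.0 to 8.5% under a nested structure, with SEs 5 to 10% too small (1500 trials per scenario, unequal unit sizes). There, Kauermann-Carroll with t on 34 degrees of freedom gave 4.9 to 5.9%.
- 6.6 to 8.0%, with SEs about 4 to 8% too small. Corrected SEs with t limits gave about 4 to 6%.

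Taken together for 36 units: roughly 6.5 to 9% type I error, with SEs about 4 to 11% too small.

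**The case against.** The strongest reply is that the article never calls these SEs ordinary or uncorrected. Kauermann-Carroll and Mancl-DeRouen estimators are themselves robust SEs, so the sentence is compatible with the remedy. A separate SAP is to be signed off before database lock, and a correction for a sensitivity model is detail often left to it. This stands as far as it goes: a reader might infer that the protocol commits to uncorrected SEs, and the text does not show that. The error rate is therefore conditional. What remains is that the article does name a variance estimator for an analysis that will be run, and the usual meaning of that name performs poorly in this layout.

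Second, the size depends on unit-size spread and working correlation that the article does not supply. That is right, and is why a range is given. The direction does not depend on them: every uncorrected scenario exceeded 5% by clearly more than Monte Carlo error, including equal unit sizes.

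Third, a reader might infer that the trial's own type I error is inflated, or that the GEE result is needed to confirm the primary one. Neither is supported. The effectiveness rule belongs to the mixed model, the GEE analysis is offered for interpretation, and alternative correlation structures are listed as a separate sensitivity analysis.

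Fourth, no single correction is clearly best. Mancl-DeRouen with t limits was nearer 5% in the tabulated runs, but Kauermann-Carroll did well in another set. This also stands, so the choice is left open.

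**Conclusion.** The point holds as a minor, conditional one. If the GEE analysis is run with an uncorrected sandwich SE and normal limits on 36 units, its error rate is roughly 6.5 to 9% against a nominal 5%, with SEs about 4 to 11% too small. In the one scenario run with 30 units (CV 0.4, independence), it was 10.6%. These figures rest on the protocol's ICC and auto-correlation, 3-month periods, and assumed unit-size variation and working correlation. Only a sensitivity analysis is affected; the primary model, its error rate and the effectiveness conclusion are untouched.

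**What to change.** In Main analysis, and in the SAP before database lock, replace *robust SEs* with: *robust SEs with a small-sample bias correction (Kauermann-Carroll or Mancl-DeRouen, one chosen before database lock) and t-based 95% CIs with df = analysed units minus 2*. With all 36 units that is 34 degrees of freedom; with 30 it is 28.

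The cost is one phrase, a software option and wider intervals for this analysis. As a guide for 36 units and CV 0.4, the t to z ratio is 2.032 / 1.960 = 1.037. Under an exchangeable working correlation the mean SEs were 0.0796 (uncorrected), 0.0831 (Kauermann-Carroll type) and 0.0868 (Mancl-DeRouen), so intervals widen by 0.0831 / 0.0796 × 1.037 = 1.08 or 0.0868 / 0.0796 × 1.037 = 1.13. Under independence they were 0.0925, 0.0990 and 0.1065, giving 1.11 or 1.19. Most of that is width the uncorrected interval lacked.
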